### Study design

2.1

This is a parallel, triple-arm, randomized, sham-controlled trial designed to evaluate the clinical efficacy of the QNT and elucidate its neuroplasticity mechanisms in PD. Eligible PD patients will be randomized into three groups (1:1:1): verum acupuncture, sham acupuncture, or wait-list control. The total observation period spans 9 weeks, including a 1-week baseline, a 4-week intervention, and a 4-week follow-up. Additionally, 20 age- and sex-matched healthy controls (HCs) will be recruited to provide normative reference data for baseline MRI comparisons. The HCs data will be used to establish PD-related brain alterations by comparing HCs vs. PD patients at baseline, thereby identifying disease-specific structural and functional abnormalities that may be modulated by QNT.

The protocol adheres to the Standard Protocol Items: recommendations for Intervention Trials (SPIRIT (14) (Supplementary material 1) and the Standards for Reporting Interventions in Clinical Trials of Acupuncture (STRICTA) (15). A flowchart of the study design is shown in Figure 1, and assessment time points are detailed in Table 1.

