#### Clinical data analysis

2.9.1

All statistical tests will be two-tailed, with significance set at α = 0.05. Baseline demographic and clinical characteristics will be summarized descriptively by group. Baseline demographic and clinical characteristics will be summarized descriptively by group. To assess baseline comparability among the three randomized groups, one-way ANOVA (or Kruskal–Wallis test) will be used for continuous variables, and chi-square tests for categorical variables. If significant between-group differences are observed at baseline, the affected variables will be included as covariates in subsequent analyses to adjust for potential confounding. For the primary clinical outcome, no correction for multiple comparisons is applied as this is a single predefined comparison. For secondary clinical outcomes, we will apply False Discovery Rate (FDR) correction within each assessment scale. Continuous data will be analyzed via one-way ANOVA (normally distributed data) or the Kruskal–Wallis *H*-test (non-normal data), with Bonferroni-adjusted *post-hoc* comparisons. Categorical variables will be analyzed using the Pearson χ^2^ test or Fisher's exact test for unordered variables, and the linear trend χ^2^ test for ordered variables. Analysis of covariance (ANCOVA) will be employed to adjust for baseline values, age, disease duration, and levodopa equivalent daily dose where appropriate. If significant baseline differences between groups are observed after randomization, these variables will be included as covariates in the corresponding models to mitigate bias. Missing data will be handled using multiple imputation by chained equations under the missing at random assumption, with sensitivity analyses comparing imputed results to complete-case analyses. An intention-to-treat (ITT) analysis will include all randomized participants, whereas per-protocol analyses will exclude non-compliant cases (< 80% session attendance).

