#### Neuroimaging data analysis

2.9.2

Neuroimaging data will be analyzed according to standardized pipelines, with comprehensive details provided in Supplementary material 3. For VBM, the CAT12 toolbox (SPM12, version r1720; CAT12, r1720) will be used for bias correction, tissue segmentation, and spatial normalization to MNI space. Whole-brain VBM results will be reported at cluster-level family-wise error (FWE) corrected *p* < 0.05 with an initial voxel-level threshold of *p* < 0.001. Resting-state fMRI data will be preprocessed using DPABI v6.1. Preprocessing will include discarding the first 10 volumes, slice timing correction, realignment, normalization to MNI space, spatial smoothing (6-mm FWHM), nuisance regression (Friston-24 motion parameters and WM/CSF signals), detrending, and bandpass filtering (0.01–0.08 Hz). Volumes with framewise displacement (FD) > 0.5 mm will be censored using scrubbing regressors; participants with >20% censored volumes or with maximum head motion >3.0 mm translation or 3.0° rotation will be excluded. Seed-based functional connectivity will be computed using predefined seeds from the Automated Anatomical Labeling (AAL) atlas (bilateral putamen, caudate, globus pallidus, and thalamus; seed coordinates are provided in Supplementary material 3). Voxel-wise connectivity maps (Fisher's z-transformed) will be assessed using cluster-level FWE correction (voxel *p* < 0.001; cluster *p* < 0.05). To address multiple comparisons arising from testing multiple seeds, seed-level multiplicity will be controlled using false discovery rate (FDR; Benjamini–Hochberg) across seeds (*q* < 0.05). In addition, the bilateral putamen will be designated *a priori* as the primary seed of interest, whereas results from the remaining seeds will be considered secondary/exploratory and interpreted with FDR control across seeds. DTI data will be processed using DTIStudio v3.0.3 (and the NODDI toolbox in MATLAB R2013b, if applicable). Fractional anisotropy (FA), mean diffusivity (MD), radial diffusivity (RD), and axial diffusivity (AD) will be computed. Regions of interest (substantia nigra, putamen, caudate) will be manually delineated on FA color maps by two independent raters blinded to group and time point, with inter-rater reliability assessed using intraclass correlation coefficients (ICC; ICC > 0.80 required). ROI-based statistical comparisons will apply Bonferroni correction within each predefined ROI family. SWI phase images will undergo high-pass filtering (32 × 32) before manual delineation of substantia nigra (SN) area and measurement of SN pars compacta (SNc) width. NM-MRI SNc width will be measured in the dorsoventral direction on the optimal axial slice using the ADW4.6 workstation. ICC will be assessed for all manual measurements, and the average of the two raters will be used for analysis. All statistical tests will be two-tailed with significance set at *p* < 0.05 after correction.

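### Bonferroni within the ROI families (and for post-hoc arm comparisons) is valid, but Holm holds the same family-wise error and never rejects less; in the clinical section the change needs unequal-variance tests

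*Protocol article*

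**What the plan says.** Section 2.9.1 sets the general level: "All statistical tests will be two-tailed, with significance set at α = 0.05". For the three arms (section 2.1: "Eligible PD patients will be randomized into three groups (1:1:1): verum acupuncture, sham acupuncture, or wait-list control") it states "Continuous data will be analyzed via one-way ANOVA (normally distributed data"), or Kruskal–Wallis for "non-normal data), with Bonferroni-adjusted" post-hoc comparisons. It does not list the pairs; three arms give three. Nor does it say which variance model the post-hoc tests use.

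The same section gives two other multiplicity rules. One reads "For the primary clinical outcome, no correction for multiple comparisons is applied as this is a single predefined comparison". The other applies FDR within each scale for the secondary clinical outcomes. The UPDRS-III sample-size calculation in section 2.3 uses a further method, Tukey–Kramer.

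For MRI, section 2.9.2 states "ROI-based statistical comparisons will apply Bonferroni correction within each predefined ROI family". The regions named for DTI are three: "Regions of interest (substantia nigra, putamen, caudate) will be manually delineated". The rule is limited to ROI-based tests. For connectivity, "seed-level multiplicity will be controlled using false discovery rate (FDR; Benjamini–Hochberg) across seeds", and the voxel-wise maps use cluster-level FWE. Section 2.6.1 makes the MRI biomarkers primary and all clinical outcomes exploratory.

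**The concern.** Bonferroni compares every p-value with α/m. Holm compares the smallest with α/m, the next with α/(m − 1), and so on, stopping at the first failure. It needs no further assumption, holds the same family-wise error, and can only add rejections.

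With exactly three arms there is a second option. Any two pairwise null hypotheses together imply the global null, so a 5% omnibus test followed by each pair at 5% is a closed procedure. It holds 5% family-wise error, provided that each test is valid. Dividing by three after the omnibus test pays again for protection already in place.

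What is at stake is power in a trial with about 20 evaluable patients per arm. That size comes from an imaging convention and not from a power calculation for any MRI effect. The ROI rule sits inside the primary endpoint, so the exploratory status of the clinical outcomes does not dispose of the point.

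**Working it through.** **Inputs.** From the document: two-sided α = 0.05; three arms, 1:1:1; 69 patients, 23 per arm; 10% attrition; UPDRS-III changes 14.0 ± 9.94, 2.84 ± 3.08 and 2.3 ± 3.0; three named DTI regions. Assumed, because the document gives no MRI effect size: standardised differences of 0.5, 0.8 and 1.0, equal SDs unless noted, and correlation 0 or 0.5 between regions.

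**The plan's own figures.** 20/(1 − 0.10) = 22.2, rounded up to 23; 23 × 3 = 69. This reproduces. The UPDRS-III figure of 165 (165 × 0.8 = 132, or 44 per arm) does not reproduce from the stated means and SDs. That is a separate matter, and nothing below uses it.

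**Thresholds for three tests.** Bonferroni: 0.05/3 = 0.0167 for each. Holm: 0.0167, 0.025, 0.05 in order. Closed test: omnibus p ≤ 0.05, then each pair at 0.05.

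**ROI family of three** (20 per arm, effect 0.8 SD, independent regions; 100,000 simulated trials). Average power per affected region:

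| Regions affected | Bonferroni | Holm |
|---|---|---|
| 3 of 3 | 0.516 | 0.603 |
| 2 of 3 | 0.515 | 0.550 |
| 1 of 3 | 0.515 | 0.518 |

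At correlation 0.5 the Holm figures are 0.597, 0.548 and 0.519. Holm's family-wise error is at most 0.043 in these runs.

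**Arm comparisons, equal SDs** (20 per arm, verum differing equally from both other arms, pooled-variance tests; 200,000 to 300,000 simulated trials). Power per true pair:

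| Effect (SD) | Bonferroni | Holm | Closed |
|---|---|---|---|
| 0.5 | 0.20 | 0.21 | 0.26 |
| 0.8 | 0.53 | 0.56 | 0.64 |
| 1.0 | 0.75 | 0.79 | 0.85 |

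At 0.8 SD, power to show both true pairs is 0.37, 0.43 and 0.55. With Welch tests throughout, power per pair at 0.8 SD is 0.51, 0.55 and 0.62. Family-wise error under the global null is 0.043 for Bonferroni and Holm, and 0.050 for the closed test.

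**Arm comparisons, the plan's SDs (9.94/3.08/3.0), 20 per arm.** Family-wise error:

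| Procedure | All arms equal | Verum = sham, wait-list differs by 10 points |
|---|---|---|
| Bonferroni, pooled | 0.062 | 0.045 |
| Holm, pooled | 0.062 | 0.099 |
| Closed, pooled | 0.076 | 0.100 |
| Bonferroni, Welch | 0.039 | 0.017 |
| Holm, Welch | 0.039 | 0.046 |
| Closed, Welch | 0.050 | 0.050 |

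The pooled SD averages one large and two small variances, so it understates the error of any contrast that involves verum.

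**The plan's own UPDRS-III effects.** Verum versus sham power: pooled tests 0.995 (Bonferroni), 0.997 (Holm), 0.998 (closed); Welch tests 0.982, 0.988, 0.992.

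**The case against.** The strongest reply is that nothing here is wrong. Bonferroni is valid and conservative, and a preference for a more powerful procedure is an optimisation. That stands, and it sets the weight of the point. Four stronger readings are tempting, and the document does not support them.

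- *Any omnibus-then-pairs scheme recovers the power at 5%.* It does so only if each test is valid. The plan names one-way ANOVA, which pools variances, and its own SDs differ about threefold. Pooled closed testing or pooled Holm then reaches about 10% when verum equals sham and wait-list differs. Part of the margin that Bonferroni leaves is protective there. Pooled Bonferroni is not fully safe either, at 6.2% under the global null.
- *The whole primary MRI endpoint loses power.* Bonferroni covers only ROI-based comparisons. Family sizes beyond the three named regions are not given in the article, and detailed thresholds are left to Supplementary material 3, which is not shown.
- *The clinical comparisons lose about 11 points of power.* That rests on an assumed 0.8 SD effect with equal SDs. At the planned UPDRS-III effects, power is at least 0.98 under every rule.
- *The primary clinical outcome is affected.* Section 2.9.1 says that it gets no correction, so it is unclear whether the Bonferroni rule reaches it.

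**Conclusion.** The point holds as a minor improvement. For the ROI families it is unconditional in direction: Holm controls the same error and never rejects less. Its size depends on how many regions are affected, from about 9 points of power (all three) through 3 to 4 points (two) to almost nothing (one), under an assumed 0.8 SD effect at 20 per arm.

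For the arm comparisons the gain is about 3 points with Holm and about 11 with a closed test at the same assumed effect. It comes at a true 5% error rate only with tests that are valid under unequal variances. It concerns exploratory outcomes, and it is negligible if the planned UPDRS-III effects are real. The choice of Bonferroni is not an error.

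**What to change.** **Section 2.9.2.** Replace Bonferroni by Holm within each predefined ROI family. Leave the seed and voxel-wise rules as they are.

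**Section 2.9.1.** Where the post-hoc rule applies, use one of these two:
- Holm across the three Welch pairwise tests; or
- a Welch omnibus test at 5% and, only if it is significant, each Welch pairwise test at 5% (closed procedure for three groups).

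Name the unequal-variance tests explicitly. Asking only for the same variance model in both steps would still admit pooled tests. If the rank-based route is kept, the same caution applies: with the plan's SDs, its closed version reached about 7% family-wise error.

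**Scope.** State which clinical outcomes this rule covers, so that it agrees with the sentences on no correction for the primary clinical outcome and on FDR for the secondary ones.

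**Cost.** Wording only, with no new data; it should be fixed before unblinding. One small downside is that simultaneous confidence intervals no longer match the tests, so report unadjusted 95% intervals and label them as such.

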### Sample size

2.3

This trial is designed as an exploratory mechanistic study, with the primary objective of detecting QNT-induced neuroplasticity using multimodal MRI. The sample size was therefore determined based on neuroimaging methodology standards. Given the lack of standardized methods for sample size estimation in acupuncture-related neuroimaging trials, we referenced fMRI studies that recommended ≥20 participants per group for robust statistical analysis (17). Accounting for a 10% attrition rate, 69 PD patients (23 per group) and 20 HCs will be enrolled. HCs undergo baseline MRI only, minimizing dropout risk. Separately, a formal power calculation for the UPDRS-III was performed using PASS 15.0. Based on our pilot data (7), the expected changes (mean ± SD) are: verum acupuncture group 14.0 ± 9.94, sham group 2.84 ± 3.08, and wait-list group 2.3 ± 3.0 (18). With α = 0.05, power = 0.90, 1:1:1 allocation, and Tukey–Kramer correction for multiple comparisons, the required sample size is 165 patients (55 per group) after adjusting for 20% dropout. This trial, however, is designed as an exploratory mechanistic study; the smaller sample of 69 patients is adequately powered for the primary neuroimaging endpoints, whereas all clinical efficacy analyses are considered exploratory and will inform the design of future large-scale multicenter trials.

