### Randomization, allocation, concealment and blinding

2.4

Randomization will be generated with the use of a random-number method via a computerized central randomization system. Eligible PD patients will be allocated in a 1:1:1 ratio to three groups: verum acupuncture, sham acupuncture, or waitlist control. After confirming eligibility, investigators will request group assignment via the centralized system, which automatically assigns and communicates the allocation to the investigator for intervention implementation. The randomization sequence will remain concealed on a secure server until completion of participant enrollment, data collection, and analysis to prevent selection bias.

To ensure methodological rigor, blinding will be implemented between the verum and sham acupuncture groups via a sham placebo acupuncture device (SPAD; Patent No. 2023215153288). The participants in both groups will receive treatments in private rooms to prevent cross-group communication. Outcome assessors, independent third-party personnel blinded to group allocations, will conduct all the clinical evaluations. A primary blinding code will be applied to the statistical database, ensuring that statisticians remain unaware of group assignments during analysis.

Owing to the inherent nature of acupuncture interventions, full blinding between acupuncture groups (verum/sham) and the wait-list control group is unattainable. However, stringent separation of study phases (recruitment, intervention, assessment) and adherence to predefined standard operating procedures (SOPs) minimize bias risks. In cases of serious adverse events (SAEs) requiring urgent unblinding (e.g., life-threatening complications), the principal investigator will access the allocation code via a sealed envelope stored in a secure location, document the reason, and report to the ethics committee within 24 h. Post-trial, the success of participant blinding will be evaluated via structured questionnaires. If blinding is compromised, we will perform sensitivity analyses by including blinding success as a covariate in the primary outcome models to assess its impact on treatment effect estimates.

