### Safety assessments

2.7

All adverse events (AEs), including symptom severity, onset time, interventions, outcomes, and follow-up details, will be documented in CRFs. For SAEs leading to participant withdrawal, a dedicated withdrawal form will record the reason, last treatment date, completed assessments, and SAE resolution status. All SAEs will be reported promptly to the institutional review board, principal investigator, and trial coordinator. AE causality will be assessed, and all events will be monitored until resolution or stabilization. Reporting will adhere to CONSORT guidelines for non-pharmacological trials.

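### Ordered categorical variables get a linear trend chi-square across three arms that have no stated order, so the result depends on how the arms are numbered (minor)

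*Protocol article*

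**What the plan says.** Section 2.9.1 (Clinical data analysis) chooses the categorical test by the type of the outcome variable alone. Unordered variables get Pearson's chi-square or Fisher's exact test. When the categories have an order, the test named is "the linear trend χ^2^ test for ordered variables". Section 2.4 says that patients are "allocated in a 1:1:1 ratio to three groups: verum acupuncture, sham acupuncture, or waitlist control". No section ranks these arms or scores them.

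Three other statements in 2.9.1 bear on the point:
- Categorical variables in the baseline comparability check get plain chi-square tests, not the trend test.
- Bonferroni-adjusted post-hoc comparisons are attached to continuous data. None is stated for categorical data.
- "All statistical tests will be two-tailed, with significance set at α = 0.05".

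Section 2.4 also says that the analysis database carries a blinding code, so that the statisticians do not know which group is which.

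**The concern.** An ordered outcome is not enough to justify a trend test on a three-row table. The linear trend chi-square measures linear association between an arm score and a category score, so both margins must be ordered. Here the columns are ordered and the rows are three different treatments. Its null hypothesis is that the outcome does not rise or fall linearly with the arm number. The trial asks whether the arms differ and, according to the Discussion, wants to separate specific effects from placebo, which is the verum-sham contrast.

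Two consequences follow. The same data can give different p-values under different numberings. And whichever arm sits in the middle drops out of the contrast, with no post-hoc step stated to recover it.

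**Working it through.** **Inputs from the protocol.** Section 2.3 starts from 20 per group and states: "Accounting for a 10% attrition rate, 69 PD patients (23 per group) and 20 HCs will be enrolled". Check: 20 / (1 − 0.10) = 22.2, rounded up to 23; 3 × 23 = 69. This reproduces. Alpha is 0.05, two-sided. The protocol gives no ordered categorical outcome, so all category proportions below are assumptions.

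**Formula.** The trend statistic is (N − 1)r², 1 df, with r the correlation of arm score and category score. With n per arm and arm scores centred at −1, 0, 1, it becomes

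(N − 1) × (T₃ − T₁)² / (2n × SS),

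where T₁ and T₃ are the category-score totals of the two end arms and SS is the total sum of squares of the category scores. The middle arm's total does not appear in the numerator; that arm enters only through SS.

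**One fixed table**, 23 per arm, category scores 1 to 4: verum 10/8/4/1; sham and wait-list identical at 3/6/8/6.
- Totals: verum 10 + 16 + 12 + 4 = 42; sham and wait-list 3 + 12 + 24 + 24 = 63 each; sum 168.
- SS = (94 + 195 + 195) − 168²/69 = 484 − 409.04 = 74.96.
- Order verum, sham, wait-list: 68 × (63 − 42)² / (46 × 74.96) = 8.70, p = 0.003.
- Order sham, verum, wait-list: 68 × (63 − 63)² / (46 × 74.96) = 0, p = 1.00.
- Tests that do not use arm codes: Kruskal-Wallis 11.66, p = 0.003; row-mean-score test 11.60, p = 0.003 (both 2 df).

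**Simulated rejection rates, set A** (4,000 trials, 23 per arm; reference 70/20/7/3%, shifted 30/35/20/15%; sham 50/28/13/9% in the graded case). V, S, W are verum, sham, wait-list in code order.

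| Truth | Trend V-S-W | Trend S-V-W | Trend V-W-S | Kruskal-Wallis |
|---|---|---|---|---|
| No difference | 0.046 | 0.046 | 0.048 | 0.044 |
| Verum-only shift | 0.833 | 0.014 | 0.822 | 0.872 |
| Sham-only shift | 0.016 | 0.838 | 0.830 | 0.870 |
| Verum = sham, both shifted | 0.777 | 0.762 | 0.054 | 0.853 |
| Graded | 0.799 | 0.237 | 0.276 | 0.731 |

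**Set B** (20,000 trials; reference 15/25/35/25%; shifts defined by a common odds ratio; comparator is the row-mean-score test).
- Verum-only shift, odds ratio 5: 0.83 in the listed order, 0.036 with verum in the middle, 0.86 for the comparator.
- Verum-only shift, odds ratio 3: 0.53, 0.043 and 0.54.
- No difference: 0.048 to 0.049 under every coding.
- Graded effect (sham √5 ≈ 2.2, verum 5): 0.84 in the listed order against 0.75. A direct verum-sham test rejects in only 0.31 of these trials, so a significant trend in the listed order is not evidence of verum against sham.

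**The case against.** The strongest reply is that the clause has no stated target. UPDRS-III, NMSS, PDQ-39, the expectancy scale and the visual analogue scales are scores, and the biomechanical data are quantitative. The blinding questionnaire is completed only in the verum and sham groups, and with two arms the trend test does not depend on coding. This stands, and it is the main reason for the low severity.

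A reader might infer that Hoehn-Yahr stage would be tested this way. The text does not support that: the stage appears only as an eligibility criterion, and baseline categorical variables fall under the plain chi-square sentence. A reader might also infer that an adverse-event excess confined to verum would be missed. Section 2.7 records "All adverse events (AEs), including symptom severity", but it states no grading scale and no between-arm test of severity. Such a use is possible, not planned.

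A second reply is that the arms are consistently listed as verum, sham, wait-list, and that in this order a verum-only shift is still found with little loss. That is right. It leaves sham with zero weight, however, and the protocol does not say that the listed order supplies the scores. Because the statisticians work on coded groups, they would need that order given to them. If the masked codes fell at random (an assumption), set A power for a verum-only shift would average (0.833 + 0.014 + 0.822) / 3 = 0.56 against 0.87.

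A third reply is that an order can be argued, since section 2.3 expects UPDRS-III changes of 14.0, 2.84 and 2.3 for verum, sham and wait-list. Those figures do rank the arms, but the gaps are 11.16 and 0.54. That is close to a verum-only pattern, where the 2-df test does at least as well. The protocol does not present them as arm scores.

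Finally, the sentence does not say that the test is run on all three arms at once. If it were used only pairwise, the fault would disappear. Nothing in 2.9.1 says so.

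**Conclusion.** The point holds as a minor one. As written, section 2.9.1 selects a test whose result over three nominal arms depends on an unstated numbering. In the listed order that test is silent on verum versus sham.

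The size is limited. Type I error is held under every coding. In the listed order the loss for a verum-only shift is 2 to 4 points under the assumed proportions (0.833 against 0.872; 0.83 against 0.86; 0.53 against 0.54). A near-total loss needs verum in the middle position, or a difference confined to sham under the listed order. The tempting stronger reading, that the trial will probably miss a verum effect on ordered outcomes, is not supported: the protocol neither names such an outcome nor places verum in the middle. The primary MRI endpoint and the UPDRS-III total are not touched, and all clinical outcomes are declared exploratory.

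The power figures rest on assumed four-category distributions and 23 analysed per arm. The dependence on coding and the zero weight of the middle arm follow from the formula and need no such assumption beyond equal arms.

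**What to change.** In section 2.9.1 replace the trend-test clause with wording such as: *ordered categorical variables will be compared across the three arms by the Kruskal-Wallis test, followed by Bonferroni-adjusted Wilcoxon rank-sum tests of verum vs sham, verum vs wait-list and sham vs wait-list.* The row-mean-score test is an acceptable alternative; it is equivalent to Kruskal-Wallis when rank scores are used. This matches the adjusted post-hoc step already stated for continuous data and still uses the ordering of the outcome.

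If the sponsor prefers the trend test, the arm order and scores should be prespecified with a reason, and a separate verum-sham comparison named.

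The cost is one sentence and no new data. The downside arises only if effects are truly graded and the arms are coded in that order: power falls from 0.80 to 0.73 in set A and from 0.84 to 0.75 in set B, that is 7 to 9 points.

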##### Patient compliance assessment

2.6.3.4

Patient compliance will be recorded at the end of the treatment. Dropouts and reasons will be documented during the 8-week observation period.

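### The only missing-data sensitivity analysis compares imputation under missing at random with complete cases, and agreement between the two cannot test that assumption for the week-4 UPDRS-III change

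*Protocol article*

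**What the plan says.** Section 2.9.1 (Clinical data analysis) fixes two things:

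- Method and the check on it: missing data are imputed by chained equations "under the missing at random assumption, with sensitivity analyses comparing imputed results to complete-case analyses". No other missing-data sensitivity analysis is named.
- Populations: "An intention-to-treat (ITT) analysis will include all randomized participants", while a per-protocol analysis leaves out patients who attended fewer than 80% of sessions.

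Table 1 and section 2.6.1.1 place UPDRS-III at baseline, week 4 and week 8. Section 2.6.1.1 makes the change from baseline to week 4 the primary clinical outcome. Sections 2.3 and 2.6.1 declare all clinical outcomes exploratory, with MRI change as the primary endpoint. Section 2.3 adds that the clinical results will inform later, larger trials.

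On patients who leave, section 2.6.3.4 says "Dropouts and reasons will be documented during the 8-week observation period". For SAEs leading to withdrawal, section 2.7 says "a dedicated withdrawal form will record the reason, last treatment date, completed assessments, and SAE resolution status". Neither passage says whether outcomes are collected after sessions stop. The article does not list the variables in the imputation model.

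**The concern.** A sensitivity analysis for missing data should vary the assumption that cannot be checked from the data. Here that assumption is missing at random. A complete-case analysis does not vary it in a useful way. With a single post-baseline score at the time of the primary clinical outcome, a patient lost before week 4 contributes no UPDRS-III information on response. A model with arm and baseline variables fills the gap from observed patients in the same arm. The complete-case analysis uses those same observed patients. The two will tend to agree whether or not the lost patients fared worse.

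Departures from missing at random are plausible. Wait-list patients know that they receive no acupuncture, and section 2.7 foresees withdrawal because of SAEs. At stake is the size of the verum-sham difference in UPDRS-III that is carried into the planning of later trials, and a statement of robustness that the planned comparison could not support.

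**Working it through.** **Inputs (section 2.3).** Expected UPDRS-III change: verum 14.0 (SD 9.94), sham 2.84 (SD 3.08), wait-list 2.3 (SD 3.0). Attrition is 10% for the enrolled sample of 69 and 20% in the separate UPDRS-III calculation.

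**The plan's own figure.** 20 / (1 − 0.10) = 22.2, rounded up to 23 per group; 3 × 23 = 69. This reproduces. At 10%, about 0.10 × 23 = 2.3 patients per arm are lost.

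**Planned difference.** 14.0 − 2.84 = 11.16 points.

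**Bias if arm is in the imputation model and stoppers are unobserved.** Let d be the share lost and f the fraction of the verum-sham difference that verum stoppers keep. The value of f is an assumption, as the article gives none. The effect in all randomised patients, whatever treatment they completed, is

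11.16 × [1 − d(1 − f)].

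Imputation within arm under missing at random targets 11.16. The overstatement is therefore d(1 − f) × 11.16:

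| d | f | Effect in all randomised | Overstatement |
|---|---|---|---|
| 10% | 0 | 10.04 | 1.12 (11% of 10.04) |
| 10% | 0.5 | 10.60 | 0.56 (5%) |
| 10% | 1 | 11.16 | 0 |
| 20% | 0 | 8.93 | 2.23 (25% of 8.93) |
| 20% | 0.5 | 10.04 | 1.12 (11%) |
| 20% | 1 | 11.16 | 0 |

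**Would the planned check show it?** A simulation used 23 per arm, 1,000 trials, 10 imputations, equal random dropout in each arm and no covariates. With f = 0 it gave:

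| d | Complete-case | Imputed, arm in model | True effect in all randomised |
|---|---|---|---|
| 10% | 11.16 | 11.16 | 10.09 |
| 20% | 11.18 | 11.16 | 8.88 |

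The two planned analyses agree, and both miss the loss. True values differ slightly from the formula through simulation error.

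**If arm is left out of the imputation model.** Lost patients in both arms are drawn from the same pooled mean, so the estimate is (1 − d) × 11.16: 10.04 at 10% and 8.93 at 20% (simulated about 10.1 and 8.9). With f = 0 this happens to match the true effect. With f = 0.5 or 1 it is too small, by 0.56 or 1.12 points at 10%. The planned comparison would then show a gap, but one of d × 11.16 whatever f is. It reflects the omitted variable and is not a test of missing at random.

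**Per-protocol analysis.** 80% of 8 sessions is 6.4, so patients with fewer than 7 sessions are excluded. This removes low attenders and makes no alternative assumption about unobserved outcomes.

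**The case against.** The tempting stronger reading is that patients who stop are no longer assessed, are imputed as if still on treatment, and that the ITT effect of verum is therefore overstated. The document does not support this.

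- The form in section 2.7 is a safety record for withdrawals caused by SAEs. Section 2.6.3.4 does not say that assessments end. Table 1 ties UPDRS-III to study weeks and not to attendance. Separating ITT from per-protocol by attendance suggests that some low attenders will have observed outcomes.
- Whether imputation treats stoppers as if they had completed depends on a model that the article does not describe. An article may leave that, and follow-up rules for stoppers, to a fuller document, so neither silence is a finding.
- The upper figures are a worst case: every stopper unobserved, arm in the model and the whole specific effect lost. The 20% rate comes from the separate calculation, not from the plan for 69 patients.
- The largest shift at 10% is about half a standard error: √[(9.94² + 3.08²) / 23] = 2.17, and 1.12 / 2.17 = 0.51. On the planning figures it would change the size of the effect and not its presence (10.04 / 2.17 = 4.6).
- The known assignment of wait-list patients bears on wait-list dropout, not on the verum-sham contrast quantified here.
- The outcomes are exploratory, and the rule stands in the clinical section. It does not bear directly on the MRI endpoint.

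All of this stands. It removes any flat claim of overstatement and lowers the weight of the point. It does not rescue the check itself, which the article names and which cannot detect data missing not at random.

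**Conclusion.** The narrow point holds. The only missing-data sensitivity analysis that section 2.9.1 states relies on essentially the same assumption as the main analysis, and the per-protocol analysis does not fill the gap. If arm is in the imputation model, stoppers are unobserved and they lose some or all of the specific effect, the verum-sham difference in UPDRS-III change would be too large by 0 to about 1.1 points at 10% attrition, or 0 to about 2.2 at 20%, with no sign of it in the planned comparison. If stoppers keep the whole effect there is no such bias, and with another imputation model the direction can reverse. Severity is minor because the clinical outcomes are exploratory. It is still worth correcting, since this is the designated primary clinical outcome and its estimate is meant to feed later trials.

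**What to change.** In section 2.9.1, keep the complete-case analysis as a supplementary analysis and add, as the sensitivity analysis for departures from missing at random, a delta-adjusted (tipping-point) analysis of the week-4 UPDRS-III change. Imputed changes in verum dropouts are made less favourable by a shift δ, for instance from 0 to 11.16 points, and the result is reported across that range. In the setting worked above the estimate becomes 11.16 − d × δ, so δ = 11.16 at 10% gives 10.04. Shifts in the other arms can be varied separately.

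Reference-based imputation, for example verum dropouts imputed from the sham arm, is an optional addition. In the simulation it gave about 10.0 to 10.1 at 10% dropout and 8.9 to 9.0 at 20%.

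The cost is a sentence or two of text and a few more analysis runs, with a sensitivity estimate that may be less favourable. No new visits or data are needed.
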